### Sampling

Six GP practices will be recruited from rural Devon and from each of the cities of Exeter and Plymouth, UK. A minimum practice size of 3000 patients will ensure sufficient numbers of eligible participants. (It is anticipated that there will be approximately 800 older patients with multimorbidity in an average 8000 patient practice [1]). Table 1 shows the participant inclusion and exclusion criteria. An average of three (total = 18 GPs), and at least 2, GPs per practice will be recruited. Patients aged 65 and above with known multimorbidity, defined as the presence of two or more long-term conditions (as specified in Table 1), will be approached.

**Table 1 Tab1:** Participant inclusion and exclusion criteria

Participant type	Inclusion criteria	Exclusion criteria
GPs	Only permanent GPs (partners and salaried) to avoid loss to follow-up.	Locum (sessional) GPs Trainee GPs (GPs will not be excluded based on less than full time working)
Patients	Patients aged 65 and above with known multimorbidity The condition should be one of^a^: angina or long-term heart problem; arthritis or long-term joint problem; asthma or long-term chest problem; blindness or severe visual impairment; cancer in the last five years; deafness or severe hearing impairment; diabetes; epilepsy; high blood pressure; kidney or liver disease; long-term back problem; long-term mental health problem; long-term neurological problem.	Temporary residents and vulnerable patients e.g. those recently bereaved, those with severe mental illness, severe cognitive impairment, end stage disease, communication difficulties e.g. physical impairment caused by a stroke as opposed to language barriers, a learning disability, or those unable to complete questionnaires or interviews for any other reason. (A minimum time for a condition to be ‘long-term’ will not be specified)

^a^This list was adapted from the English National General Practice Patient Survey [10]. Where dyads of conditions occur within the same organ system, e.g. anxiety and depression, these will only be counted once e.g. mental health problem

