Patient participants will be identified using an automated practice database search strategy designed by the research team. The practice administrative team will use this ‘flag’ to identify ten consecutive potential participants with pre-booked consultations with each of the three recruited GPs. Random sampling of participants is not required as the clinical presentations, and therefore the nature of the decision-making between consecutive consultations, is expected to be random. A total of 180 (minimum 120) potential patients will be identified across 6 practices, with the aim of recruiting at least half.

The sample size is sufficient to compare between-group differences in quantitative feasibility objectives such as recruitment rates and data collection procedures including the completeness of participant questionnaires. This sample size also allows the estimation of standard deviations for the clinical outcome measures being tested. In addition, it is sufficient to obtain a purposively selected sub-sample of participants for process evaluation interviews, to achieve the qualitative feasibility objectives.

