### Randomisation and blinding

The study will use a cluster randomised design. Clusters will be defined at practice level, with practices randomised 1:1 to usual care or to the intervention (90 patients per arm) following recruitment. Block randomisation will be stratified by site; two practices in inner city Plymouth, two practices from Exeter and two from rural Devon.

Randomisation will be conducted by an independent statistician who is blinded to the identity of practices. Blinding of the research team to outcome assessment will not be possible due to resource availability. Blinding of participants is unlikely to be achievable as participants in the intervention arm are likely to be aware that they are receiving more than standard ‘usual care’.

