### Analysis

#### Recruitment capability, consent and randomisation procedures, sample characteristics

The trial will determine whether it is possible to recruit appropriate study participants to test the intervention, or whether amendments are required ahead of a future trial. The flow of participants will be summarised in a Consort diagram. Numbers of eligible clusters, individual participants identified and randomised, recruitment rates and attrition will be recorded.

The search strategy used to identify potentially eligible patients will be tested on different practice databases with a view to finalising a generic, universal search algorithm. Anonymised data on ineligible patients will provide a profile of those frequently excluded. Consideration will be given to whether adaptations to the trial could be appropriate, to enable these patients to participate in a future study.

Any difficulties with meeting recruitment targets (6 practices; at least 2 GPs per practice; at least 5 patients per GP) will be documented. Field notes and correspondence with practices will enable the issues to be explored. Patients’ reasons for declining will be reviewed in light of recruitment procedures. For example, patients will use the pre-consultation questionnaire to indicate whether they received the information pack in the post. The extent to which over-recruitment is necessary will be reviewed, as will the importance of incentivising participants.

Randomisation procedures will be discussed at team meetings to inform amendments prior to a larger trial. For example, consideration will be given to randomising more practices to the intervention than to usual care, to gather more data regarding intervention implementation if required. Consideration will be given to initiating the study in each of the three sites sequentially (e.g. inner city, then urban, then rural) in order to increase trial management capacity. Consideration will be given to blinding the research team for data analysis in the future trial.

Rates of patient consent, to the use of questionnaire data, to video-recording ([12]; Asan and Montague 2014) and to case note review, will be evaluated. Numbers lost to follow-up will be reviewed; however, it is anticipated that this will be minimal. The study will determine whether there are differential drop-out or recruitment rates between intervention and control groups (indicative of selection bias).

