**Clinical outcomes**					
Putative primary outcome					
Ratings of shared decision-making during the consultation from an observer perspective.	During data analysis	Assessment of video’d consultations by two trained researchers using the OPTION(5) score ([18] [19];)	18 GPs, 180 patients (9 GPs and 90 patients per arm)	Continuous (OPTION score 0-100%)	Mean and standard deviation, to report data descriptively. Linear hierarchical modelling to estimate between group differences* (random effect on cluster, adjustment for practice location).
Additional outcomes					
Patient-reported rating of involvement in decision-making about their healthcare	Immediately following the index consultation	Patient post-consultation questionnaire—using collaboRATE score ([18] [19];)	180 patients (90 per arm)	Continuous (collaboRATE score 0–100%)	Mean and standard deviation, to report data descriptively. Linear hierarchical modelling to estimate between group differences^a^ (random effect on cluster, adjustment for practice location). Patient and GP scores compared using logistic regression modelling (patient scores as outcome, GP scores as explanatory variable).
Patient-reported rating of feeling satisfied with the healthcare received	Immediately following the index consultation	Patient post-consultation questionnaire	180 patients (90 per arm)	Categorical, ordinal (3 point Likert scale)	Frequencies, to report data descriptively. Logistic hierarchical modelling to estimate between group differences^a^ (random effect on cluster, adjustment for practice location).
Patient-reported rating of having trust in the GP they saw				Categorical, ordinal (3 point Likert scale)	Frequencies, to report data descriptively. Logistic hierarchical modelling to estimate between group differences^a^ (random effect on cluster, adjustment for practice location).
Patient-reported rating of enablement				Discrete (PEI score 0–12)	Frequencies, to report data descriptively. Logistic hierarchical modelling to estimate between group differences^a^ (random effect on cluster, adjustment for practice location).

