Participant experiences of the intervention, participants experiences of the study	Following receipt of participant post-consultation questionnaires and consent forms	Interviews with the participants from practices assigned to the intervention	9 GPs, 15 patients	Audio-recordings for qualitative analysis	Both deductive and inductive approaches to thematic analysis

^a^Between group differences will be reported using the appropriate outcome metric with 95% confidence intervals; no p-values will be reported in this feasibility study

Using an ‘intention to treat’ approach, participants will be analysed according to their randomised allocation irrespective of intervention actually received. However, all participants will be considered adherent by definition of the protocol. There is no mechanism by which participants in the control group could receive the intervention.

An intra-cluster correlation coefficient (ICC) will be calculated within each arm (intervention and control) for academic purposes; however, this will not be used to calculate a sample size for the future definitive trial; an estimated ICC, calculated from a large relevant routine dataset, will instead be sought [40].

The appropriateness of the outcome measures for use in a future, definitive trial of the intervention will be evaluated. The consistency with which certain outcome measures (e.g. OPTION(5), CollaboRATE, and those items taken from the GPPS survey) perform with the study population, when compared with previous performance in existing literature, will be reviewed. Findings will also be considered in the context of the internal consistency of performance of these measures within the participant sample. Consideration will be given as to whether the outcome measures chosen are sensitive to the effects of the intervention in the context of older people with multimorbidity in primary care, or whether there is a need for development of new measures.

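### The arm contrast has only 2 degrees of freedom: the size does not support comparing feasibility rates between arms, and the Table 4 95% CIs can under-cover unless a small-sample method is used

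*Protocol article*

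**What the plan says.** **Design.** Randomisation and blinding has "practices randomised 1:1 to usual care or to the intervention (90 patients per arm) following recruitment", stratified by site: "two practices in inner city Plymouth, two practices from Exeter and two from rural Devon". Each site therefore contributes one practice per arm. Sampling plans three GPs per practice on average and "ten consecutive potential participants with pre-booked consultations with each of the three recruited GPs", with the aim of recruiting at least half of those identified.

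**Feasibility comparisons.** Sampling states: "The sample size is sufficient to compare between-group differences in quantitative feasibility objectives such as recruitment rates and data collection procedures". The section on recruitment capability, consent and randomisation procedures adds: "The study will determine whether there are differential drop-out or recruitment rates between intervention and control groups (indicative of selection bias".

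**Outcome comparisons.** Table 4 (Evaluation of outcome measures) assigns linear, logistic or Poisson hierarchical models, each with "random effect on cluster, adjustment for practice location". Its footnote says "Between group differences will be reported using the appropriate outcome metric with 95% confidence intervals" and rules out p-values. The protocol does not say whether the intervals use a normal or a t reference, whether estimation is by REML or ML, or whether any small-sample correction applies.

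**Disclaimers.** The section on preliminary evaluation of participant responses excludes power calculations and hypothesis tests. Strengths and limitations says that the study lacks power for the intervention effect.

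**The concern.** Treatment is assigned to practices, so information about a difference between arms comes from practices, not patients. Three site pairs provide very little of it.

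This affects two statements that should be kept apart. The first is the claim that the size is adequate for between-arm comparison of feasibility measures and will settle whether recruitment or drop-out differs by arm. The protocol treats such differences as signs of selection bias. If three pairs of practices cannot separate an arm effect from ordinary variation between practices, chance may be read as bias, or real bias may go unseen.

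The second is the set of confidence intervals in Table 4. With no p-values, these are the only inferential statement about arm differences in outcomes. If they are built with a multiplier that takes the between-practice variance as known, their true coverage may fall short of 95%.

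**Working it through.** **Stated size.** 6 practices × 3 GPs × 10 patients = 180, and 6 × 2 × 10 = 120. Both match Sampling. 180 / 2 = 90 per arm, or 30 approached per practice. Recruiting half gives 15 per practice. There is no power figure to reproduce.

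**Degrees of freedom.** 6 practices − 1 (intercept) − 1 (arm) − 2 (three locations) = 2. The 97.5% point of t on 2 df is 4.303, against 1.960 for the normal: 4.303 / 1.960 = 2.2 times as wide for the same standard error.

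**Recruitment-rate difference.** Inputs: p = 0.50 (the recruit-half aim), m = 30 approached per practice, three practices per arm. The protocol gives no ICC, so 0 to 0.10 is an assumed range.

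SE = √[2p(1−p)(1 + (m−1)ICC) / (3m)]

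- ICC 0: √(0.5/90) = 0.0745
- ICC 0.05: design effect 1 + 29 × 0.05 = 2.45, SE = 0.117
- ICC 0.10: design effect 1 + 29 × 0.10 = 3.90, SE = 0.147

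| Assumed ICC | ± with 1.96 | ± with t(2) |
|---|---|---|
| 0 | 14.6 points | 32.1 points |
| 0.05 | 22.9 points | 50.2 points |
| 0.10 | 28.9 points | 63.3 points |

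The first entry with 1.96 is what one gets by ignoring clustering altogether. The t(2) figures are planning values; the realised width will vary, because the standard error is itself estimated on 2 df.

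**A check that needs no ICC.** One practice per arm in each of three sites allows 2³ = 8 allocations. If recruitment is lower in the intervention practice at all three sites, that pattern or its mirror image arises by chance in 2/8 = 25% of allocations.

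**Coverage of a nominal 95% interval, linear model.** Balanced random-intercept data for six practices in three site pairs were simulated, with closed-form REML and ML variance estimates (between-practice component truncated at zero) and 500,000 draws per cell.

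| Patients per practice | Assumed ICC | REML, 1.96 | ML, 1.96 | Practice-level, t(2) |
|---|---|---|---|---|
| 15 | 0 | 96.0% | 94.3% | 95.0% |
| 15 | 0.01 | 94.9% | 92.5% | 95.0% |
| 15 | 0.05 | 91.2% | 86.0% | 95.0% |
| 15 | 0.10 | 88.2% | 79.8% | 95.0% |
| 15 | 0.20 | 84.8% | 72.1% | 95.0% |
| 30 | 0 | 96.1% | 94.7% | 95.0% |
| 30 | 0.01 | 94.1% | 91.3% | 95.0% |
| 30 | 0.05 | 88.4% | 80.6% | 95.0% |
| 30 | 0.10 | 85.2% | 73.4% | 95.0% |
| 30 | 0.20 | 82.9% | 67.4% | 95.0% |

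A REML standard error combined with t(2) covers 97.4% to 100% over the same range, so it is conservative and not the same as the practice-level method. With 15 per practice and ICC 0.05, REML puts the between-practice variance at zero in about 43% of trials.

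The logistic and Poisson models were not simulated.

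**The case against.** The best reply is that the protocol never specifies the interval under criticism. It names models and a confidence level. The reference distribution is a detail usually left to an analysis plan, which is not shown here. A reader might infer that the planned Table 4 intervals do under-cover. The document does not support that: no large-sample multiplier is stated, the ICC is not given, and at ICC 0 to 0.01 even the uncorrected REML interval covers about 94% to 96%. This objection stands, and the second point is conditional for that reason.

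It is also fair that the two points are distinct. Recruitment and drop-out are not assigned a hierarchical model or an interval, so weak coverage in Table 4 would not by itself show that the Sampling statement is wrong. That statement has to fail on its own precision, as calculated above.

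The harm is limited too. The study disclaims power and testing for effect, the progression criteria rest on recruitment and data-collection rates and not on arm contrasts, and the ICC for the definitive trial is to come from an external dataset.

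These disclaimers do not reach the first point. They concern the intervention effect and hypothesis tests. The statements about comparing feasibility measures and establishing differential recruitment carry no such qualification, and an unseen analysis plan cannot supply clusters that the design lacks.

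**Conclusion.** The concern holds in two parts of different strength.

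1. **Feasibility comparisons: not supported as written.** A half-width of about 15 points is the most favourable figure, and it ignores clustering. With t(2) it is about 32, 50 and 63 points at ICC 0, 0.05 and 0.10. This assumes a 50% rate, 90 approached per arm and balanced practices. A study of this size can describe arm differences in recruitment or drop-out; it cannot settle whether they exist.

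2. **Table 4 intervals: at risk, conditionally.** If linear REML models are used with the usual large-sample multiplier, coverage is about 91% to 85% (15 per practice) or 88% to 83% (30 per practice) at assumed ICCs of 0.05 to 0.20, and close to nominal at 0 to 0.01. ML would be worse. The figures apply to balanced linear models only.

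This is a matter for correction of wording and method. It does not undermine the feasibility design or its progression criteria.

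**What to change.** - **Sampling:** limit the sufficiency statement to overall rates and to estimating standard deviations.
- **Recruitment analysis:** say that between-arm differences in recruitment, drop-out and completeness will be described, and give the expected half-width with its assumed ICC range.
- **Table 4 footnote:** for continuous outcomes, and for binary or count outcomes that are not sparse, take the difference between the intervention and control practice summaries within each site. Report the mean of the three differences ± 4.303 × (their standard deviation / √3), which is t on 2 df.
- **Alternative for linear models:** name a small-sample correction such as Kenward-Roger. It is not identical to the practice-level method: it may be conservative, and its result may depend on the software when the between-practice variance is estimated as zero. The plan should therefore say what is done in that case.
- **Sparse outcomes such as deaths:** report descriptively by arm, without a model-based interval.

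The cost is wider intervals and some changes of wording. No extra data are needed.

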#### Evaluation of resources and capacity to manage the study and implement the intervention

A cost-effectiveness framework for a subsequent definitive trial will be developed by identifying, measuring and valuing the resources used to deliver the intervention. For example, the time required to identify ten consecutive eligible patients per GP will contribute to informing the time required for intervention delivery in the future trial. Data collection processes will be tested with consideration of estimations of the size and range of cost components, along with reporting of the resource use categories prone to missing data. For example, the acceptability of administering questionnaires will be analysed by reporting missing values and presenting mean scores and 95% confidence intervals.

Patient safety data will be described numerically in both intervention and control practices (no hypothesis testing), e.g. hospital admissions, attendances at A&E and deaths within 7 days of the index consultation.

#### Preliminary evaluation of participant responses to the intervention

The intended sample size is sufficient to estimate standard deviations in our intended primary outcome, ‘ratings of shared decision-making during the consultation from an observer perspective’, for the intervention and control group. This outcome data will be obtained from OPTION(5) ratings of video-recorded consultations. No formal power calculations will be carried out and hypothesis testing will not be appropriate [47].

The observer OPTION(5) scores (Elwyn 2014) and the patient and GP ratings of shared decision-making, based on collaboRATE (Elwyn 2014), will be analysed using hierarchical linear modelling with a random effect on cluster. Patient and GP collaboRATE scores will be compared using logistic regression; modelling patient scores as the outcome and GP scores as the explanatory variable, providing preliminary data on whether patient and GP perceptions are congruent.

Patients vary in their pre-existing preferences for involvement in decision-making about their healthcare (Butterworth 2013 [50];). A secondary analysis with adjustment for patients’ reported preference for shared decision-making will provide a preliminary indication as to whether patients’ pre-existing preferences influence the effect of the intervention.

The participant population will be ‘all randomised’ and the analysis strategy will be ‘intention to treat’. There are no plans for interim analysis.

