GP-reported rating of their involvement of the patient in decision-making about their healthcare	Immediately following the index consultation, after confirming patient consent for each aspect of data collection.	GP questionnaire using adapted collaboRATE ([18] [19];)	18 GPs (9 per arm)	Continuous (collaboRATE score 0-100%)	Mean and standard deviation, to report data descriptively. Linear hierarchical modelling to estimate between group differences^a^ (random effect on cluster, adjustment for practice location). Patient and GP scores compared using logistic regression modelling (patient scores as outcome, GP scores as explanatory variable).
Patient contacts in a 28-day period following the index consultation, including the nature of contact with the GP surgery, the hospital admissions, A&E attendances. If patient moved away within 28 days (i.e. lost to follow up)	Approximately 12 weeks after index consultation (to allow time for contacts to be recorded in the notes)	Case note review by two researchers	180 patients, (90 per arm)	Count	Median and range, to report data descriptively. Poisson hierarchical modelling to estimate between group differences^a^ (random effect on cluster, adjustment for practice location).
Deaths within a seven day period following the index consultation; death within 28 days (i.e. did not have full study follow-up).	Approximately 12 weeks after index consultation (to allow time for contacts to be recorded in the notes)	Case note review by two researchers	180 patients, (90 per arm)	Count	Median and range, to report data descriptively. Poisson hierarchical modelling to estimate between group differences^a^ (random effect on cluster, adjustment for practice location).
Documented decision outcomes from the index consultation, e.g. starting/stopping/changing medication, referrals and investigations	Approximately 12 weeks after index consultation (to allow time for contacts to be recorded in the notes)	Case note review by two researchers	180 patients, (90 per arm)	Binary (yes/no) variables for each type of change	Frequencies, to report data descriptively. Logistic hierarchical modelling to estimate between group differences^a^ (random effect on cluster, adjustment for practice location).
Process evaluation					

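### The patient-GP collaboRATE comparison has no GP effect and no arm term, so its single slope cannot be read cleanly as congruence (minor)

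*Protocol article*

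**What the plan says.** The comparison appears three times in the protocol article: once in the section on preliminary evaluation of participant responses, and once each in the patient-reported and GP-reported involvement rows of Table 4. The text reads "Patient and GP collaboRATE scores will be compared using logistic regression; modelling patient scores as the outcome and GP scores as the explanatory variable". Both table rows read "Patient and GP scores compared using logistic regression modelling (patient scores as outcome, GP scores as explanatory variable". Its stated purpose is preliminary information on whether the two parties' perceptions agree.

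The neighbouring models are described differently. In the sentence just before, the observer, patient and GP ratings "will be analysed using hierarchical linear modelling with a random effect on cluster". Where Table 4 intends a clustered logistic model, it says so: "Logistic hierarchical modelling to estimate between group differences^a^ (random effect on cluster, adjustment for practice location".

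On data structure, "Clusters will be defined at practice level". The GP score comes from "18 GPs (9 per arm" in total, and each rating is made "Immediately following the index consultation, after confirming patient consent for each aspect of data collection". The Sampling section identifies "ten consecutive potential participants with pre-booked consultations with each of the three recruited GPs".

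**The concern.** Each patient contributes one rating, while the same GP contributes a rating for every consultation. The explanatory variable therefore carries that GP's habitual generosity or severity towards their own performance. A slope fitted across all consultations blends the within-GP association (does the GP's rating rise in those consultations that the patient also rates higher?) with the between-GP association (do GPs who rate themselves highly have patients who rate them highly?).

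The intervention trains the GP and prompts the patient, so either score may move by arm. Without an arm term, a shift in both scores becomes part of the slope.

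At stake is interpretation. A weak slope could reflect GP rating style rather than lack of agreement, and a positive slope could reflect allocation rather than agreement. A practice random effect alone would not resolve this, because the repeated rater is the GP and not the practice. Changing the model from logistic to linear would not resolve it either.

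**Working it through.** **1. The plan's counts.** Sampling gives 6 practices, an average of 3 GPs each and 10 patients identified per GP: 6 × 3 × 10 = 180. With 2 GPs per practice, 6 × 2 × 10 = 120. Both match the stated figures. Ratings per GP are 180/18 = 10, or 90/18 = 5 if half the patients are recruited. No intra-cluster correlation (ICC), arm effect or power figure is given for this comparison, so everything from step 3 on rests on assumed values.

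**2. The model as stated.** All three statements name one outcome and one explanatory variable. The between-group models in the same table cells name a random effect and a location adjustment. That the comparison is single-level and pooled over arms is an inference from this contrast; those words are not in the document.

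**3. Rating style.** Let ρ be the share of GP self-rating variance that lies between GPs, and suppose rating style is unrelated to the GPs' patient means. In a linear model only the within-GP part then contributes covariance, so

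pooled slope = within-GP slope × (1 − ρ).

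This gives a slope lower by 5% at ρ = 0.05, 20% at 0.2, 40% at 0.4 and 60% at 0.6. Logistic simulations agree (about 6% at ρ = 0.05). With 18 GPs, patient score split at its middle, patient-score ICC 0.1 and within-GP correlation 0.4 (1,500 runs per setting), the log-odds slopes per SD are:

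| ρ | Ratings per GP | Pooled | Within GP | Pooled lower by |
|---|---|---|---|---|
| 0.3 | 5 | 0.58 | 0.85 | about 31% |
| 0.3 | 10 | 0.57 | 0.83 | about 32% |
| 0.5 | 5 | 0.50 | 1.01 | about 51% |
| 0.5 | 10 | 0.49 | 0.98 | about 50% |

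With within-GP correlation 0.3, patient ICC 0.05 and ρ = 0.4, the slopes are about 0.40 and 0.66.

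The gap depends on the scale. With those last inputs, the pooled correlation is 0.3 × √(0.6 × 0.95) = 0.23, about 25% below 0.30 rather than 40%.

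**4. Arm shift alone.** With equal arms and shifts dP (patient) and dG (GP) in SD units, the induced covariance is dP × dG/4, and the variance of the GP score becomes 1 + dG²/4. For 0.5 and 0.5 the linear slope is 0.0625/1.0625 = 0.06 with no consultation-level association at all. In simulated logistic fits (ICCs 0.1 for patients and 0.3 for GPs):

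- Both scores shifted by 0.5 SD: pooled slope 0.11 (5 per GP) and 0.09 (10 per GP), with a 95% interval excluding zero in 11% and 13% of runs. With GP-centred score, GP mean and arm in the model, the slope is about 0.01 and 0.00, and the rate 5 to 6%.
- Patient shift 0.5 SD, GP shift 1 SD: pooled slope 0.18 and 0.17, rate 15% and 23%. With the fuller model the slope is about 0.01 and the rate 3 to 4%.

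**5. Ignored clustering alone.** For a slope, the variance inflation is roughly 1 + (m − 1) × ICC(GP score) × ICC(patient score). At 0.1 and 0.1 this is 1 + 4 × 0.01 = 1.04 for m = 5 and 1 + 9 × 0.01 = 1.09 for m = 10. At 0.5 and 0.5 it is 2.0 and 3.25. In simulation with no association and no arm shift, the interval excludes zero in about 6% of runs at ICCs 0.1 and 0.3, and in 8% (m = 5) or 12% (m = 10) at 0.2 and 0.5.

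**The case against.** The strongest reply is that this is a condensed article. The sentence names an outcome and a predictor, and arm terms, GP effects and centring for a descriptive secondary comparison could be left to an analysis plan. That holds in part for centring. It is weaker for the missing random effect, because the article states this model three times without one, next to models that do have one.

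The second reply concerns the target. A GP who always rates their own involvement above what patients report is incongruent with those patients, so rating style is arguably part of the question. This stands. A reader might infer from step 3 that the pooled slope is simply too small. The protocol never limits congruence to within-GP tracking, so the supported statement is that the slope mixes components. Nor does any slope show a constant over-rating, which needs a mean difference.

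Three further inferences are tempting and unsupported:

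- **Lost power or excess false positives.** The protocol rules out hypothesis testing, so the exclusion rates above only gauge the distortion.
- **A faulty confidence interval.** The Table 4 footnote promises 95% intervals for between-group differences; none is specified for this comparison.
- **A decision at stake.** Nothing says this result settles whether both collaboRATE versions go into the definitive trial. Measures are to be judged on performance against the literature, internal consistency and sensitivity to the intervention.

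The same sentence also applies logistic regression to a score Table 4 calls continuous. That is a separate matter, but it means the sentence needs rewriting anyway.

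**Conclusion.** The point holds as a minor one. As stated, the patient-GP comparison yields a single slope that combines consultation-level tracking, GP rating style and arm differences, and it cannot be read cleanly as congruence. The pooled slope may lie about 6% to 60% below the within-GP slope for an assumed self-rating ICC of 0.05 to 0.6. A moderate shift in both scores can produce a small association where none exists within GPs. The document gives neither the ICCs nor the shifts, and if GPs differ little in rating style the effect is slight. Ignored clustering is not the main issue unless both ICCs are high. The analysis is preliminary and secondary, and it is not among the progression criteria.

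**What to change.** When the sentence and the two Table 4 cells are rewritten, specify a hierarchical model of the patient score with a random effect for GP (within practice) and fixed effects for arm and practice location. Enter the GP score as two terms: the deviation from that GP's own mean, and the GP mean. Report both coefficients, and report the mean patient-GP difference by arm so that systematic over- or under-rating stays visible.

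The cost is a sentence or two of wording and a few lines of code, with no new data. The within-GP coefficient may have a somewhat wider interval. By-arm estimates will be imprecise, with 9 GPs per arm and about 45 patients per arm if half of the 90 are recruited. A practice variance will be poorly estimated: 6 practices less an intercept, one arm term and two location terms leave 2 degrees of freedom. The simulated comparison model had GP-centred score, GP mean and arm, but no random intercept or location term, so the precision of the full model has not been checked here.
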